### Randomization and masking

Randomization will be controlled centrally based on a predefined randomization schedule using block randomization using an Interactive Web and Voice Response System (IWRS) system maintained by an external service provider. Randomization was stratified by for regions (Japan/non-Japan). Access to the randomization list is restricted to designated people of the service provider not involved in the conduct or analysis of the trial. The treating physician (see below) transmits data critical for the randomization procedure via the IWRS system. All patients and study personnel will be blinded. Standard measures will be taken for the placebo and IgPro20 to ensure adequate blinding. A “two-physician” approach is implemented to reduce the chance of potential study unblinding. The “treating” physician will be the primary contact for the patient and will be responsible for all patient-related questions, adverse event (AE) evaluation, and for all other study-related tasks. A second “evaluating” physician will be responsible for assessment of efficacy variables. The evaluating physician does not have access to any data collected by the treating physician. For interim analysis and ongoing risk-benefit evaluations, members of the independent data monitoring committee may need to be unblinded. Access to study documents containing information on IgG levels and treatment groups will be restricted to people not directly involved in the study.

In case of an emergency and if necessary to make an adequate treatment decision, the blind can be broken by the treating physician using the interactive voice/web response system. Patients in whom the blind code has been broken will be discontinued from the study after a completion visit.

### Outcome assessment

#### Primary outcome

Primary outcome is defined as the percentage of patients who have a CIDP relapse during SC treatment or who are withdrawn from the study during SC treatment for any reason.

CIDP relapse is defined as a deterioration (i.e., increase) by at least 1 point in the total adjusted INCAT score during the SC treatment period visit compared with baseline. Baseline scores are defined as the scores assessed at the end of the IVIg restabilization period. The INCAT disability scale ranges from 0 (healthy) to 10 (unable to make any purposeful movements with arms or legs) [32].

#### Secondary outcomes

Secondary outcomes are:Between-group differences of the median changes from baseline to completion visits in INCAT score, mean grip strength for both hands separately, Medical Research Council (MRC) sum score, and I-RODSTime to CIDP relapse or withdrawal for any other reason in SC treatment periodTime to improvement on IgPro10 restabilization therapy (INCAT, I-RODS, and grip strength)Median changes before and at the end of IgPro10 restabilization or rescue therapy in mean grip strength, MRC sum score, I-RODS, and INCAT disability scoreTime to improvement after CIDP relapse in the SC treatment period with IgPro10 rescue therapy, defined as a decrease in INCAT score back to or below baseline value

Grip strength will be measured as described above. MRC sum score is determined by assessing bilateral shoulder abduction, elbow flexion, wrist extension, index finger abduction, hip flexion, knee extension, foot dorsiflexion, and great toe dorsiflexion. The MRC sum score is the sum of all 16 muscle scores and ranges from 0 (paralysis) to 80 (normal strength) [33, 34].

The I-RODS is an outcome measure that captures activity and social participation in patients with immune-mediated peripheral neuropathies [28]. The 24-item questionnaire covers a wide range of tasks of daily life that are each to be rated as “impossible to perform,” “able to perform with difficulties,” or “easily performed.” The summed raw score will subsequently be transformed to a centile score that ranges from 0 (most severe activity and social participation limitations) to 100 (no activity and social participation limitations).

#### Assessment schedule of primary and secondary outcome variables

INCAT scores, grip strength, MRC sum score, and I-RODS will be assessed at the screening visit; during the IgG dependency test period as described above, before IVIg infusion at weeks 1, 4, and 7; at baseline (weeks 10 or 13); at all visits during the SC treatment period, including the completion visit; and at any unscheduled visit.

#### Safety outcomes

Patient safety will be monitored throughout the study. AEs per infusion and number and the percent of patients with AEs will be collected for IgPro20 and for IgPro10 separately. AEs, including serious AEs, will be documented at each site visit and additionally for Japan at 4 weeks after last dose. Potential hemolysis will be assessed during the phone call on day 8 of the IVIg restabilization period. Medications will be reviewed at each site visit as well as 4 weeks after the last dose in Japan.

#### Exploratory outcomes

Nerve conduction studies will be performed in a standardized manner after appropriate warming of the extremities. An electrophysiology manual will be provided to all participating centers describing in detail all nerve-conduction-study procedures. Nerve conduction studies will be performed at baseline and at the completion visit.

Quality of life will be assessed using the EuroQoL 5-Dimension Questionnaire (EQ-5D), Treatment Satisfaction Questionnaire for Medication (TSQM), and Work Productivity and Activity Impairment Questionnaire for General Health (WPAI-GH) [35–39]. These instruments will be completed by the patients themselves at screening, baseline, SC week 9, and at the completion visit.

The EQ-5D is a simple, generic measure of health status, consisting of two components: a 0 to 100 mm visual analog scale (VAS) assessing overall health on the day of assessment and five questions covering five health dimensions [39]. The TSQM (version 1.4) is a 14-item general instrument that measures the major dimensions of satisfaction with a medication [36]. Scores on the TSQM scales range from 0 (indicating poor satisfaction) to 100 (indicating perfect satisfaction).

The WPAI-GH questionnaire was developed to measure the effect of general health and symptom severity on work productivity and regular activities [38]. A higher score on the WPAI-GH indicates greater impairment and less productivity.

Patient preference for IV or SC treatment will be assessed via a questionnaire consisting of three options: prefer current treatment [SCIg], prefer previous treatment [IVIg], and have no preference. In addition, a selection of predefined reasons for their preference will be provided. The patient preference for treatment questionnaire will be completed at SC week 9 and at the completion visit. Other exploratory outcome measures are hematology, serum chemistry, virology assessments, vital sign measurements, and physical examination.

Pharmacokinetic variables will be restricted to serum IgG levels collected at the screening visit; before the first IVIg infusions on day 1, week 1, week 4, at baseline, and at SC weeks 9 and 17; and at the completion visit. For patients who receive IVIg rescue medication, IgG levels will additionally be assessed before the first infusion of IVIg rescue medication, before the final infusion of the loading dose, and at each subsequent maintenance dose.

### Statistical analysis

#### Sample size

The study is powered to show that the percentage of patients having a CIDP relapse or withdrawing from the study during the SC treatment will be statistically significantly higher for the placebo group than for at least one of the examined IgPro20 doses arms. A monotonic dose response is expected with placebo ≥ IgPro20 low dose ≥ IgPro20 high dose.

The percentages of patients who reach an endpoint (i.e., relapse or withdraw during SC treatment) will be assumed to be 35 % for the IgPro20 high dose, 52 % for the IgPro20 low dose, and 65 % for placebo. These numbers are based on the (recalculated) data of the ICE study extension period [32], which are adopted based on differences in the study setup. The fraction of IVIg independent patients included is assumed to be 15 %; those patients are believed to have a relapse rate of 10 % regardless of treatment.

The exact Cochran-Armitage trend test with equally spaced scores has been used for the sample-size calculation. With a one-sided significance level of 2.5 %, a sample size of 58 is needed in each treatment arm to achieve a power of 90 % in an intention-to-treat analysis based on the above assumptions. Thus, the overall sample size will be 174 patients treated either with IgPro20 or placebo. Accounting for patients who will not pass the IgG dependency test and IVIg restabilization period, up to 350 patients need to be screened to ensure that 174 patients are treated with IgPro20 or placebo.

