#### Efficacy evaluation primary outcome

The exact Cochran-Armitage trend test will be used for the primary outcome. This comparison will be calculated to test for superiority of at least one IgPro20 dose over placebo at a one-sided type-I error of α = 0.025. If the hypothesized superiority is demonstrated, one-sided Fisher’s exact tests will be used for the subsequent comparisons: placebo vs. low dose IgPro20, and low dose IgPro20 vs. high dose IgPro20.

The proportions and corresponding two-sided 95 % Wilson-Score confidence intervals will be calculated for each treatment group. Point estimates for the difference in proportions and the corresponding exact two-sided 95 % confidence intervals will be calculated for all pair-wise treatment comparisons. The primary endpoint analyses, including all sensitivity analyses (see below), will be performed based on the ITTS and repeated for the PPS.

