#### Interim analyses

The independent data monitoring committee will be unblinded for a formal interim analysis based on the outcome data of at least 60 patients at SC week 12. The decision will be based on the outcome at 12 weeks in the SC treatment period rather than on the outcomes. The decision following the interim analysis will be to either stop the study for futility or to go on as planned and stop with the originally planned sample size.

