### Trial status

The trial started in March 2012 and completed patient recruiting by the end of November 2015. Currently, 289 patients have been screened, and 172 have been randomized. Study completion is expected at the end of 2016.

All items from the World Health Organization Trial Registration Data Set can be found at http://apps.who.int/trialsearch/Trial2.aspx?TrialID=EUCTR2011-003448-28-DE.

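### At 58 per arm the exact trend test named in the plan has about 88% power, not the stated 90%; the gap is minor and needs a text correction, not more patients

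*Protocol article*

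**What the plan says.** All inputs are in the protocol article.

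- Sample size, on the test: "The exact Cochran-Armitage trend test with equally spaced scores has been used for the sample-size calculation". The error rate follows: "With a one-sided significance level of 2.5" percent. The result is that "a sample size of 58 is needed in each treatment arm to achieve a power of" 90%, and so "the overall sample size will be 174 patients treated either with IgPro20 or placebo".
- Sample size, on the rates: 35% on high dose, 52% on low dose and 65% on placebo reach the endpoint of relapse or withdrawal. The same paragraph assumes that 15% of included patients are IVIg-independent and relapse at 10% in every arm.
- Efficacy evaluation primary outcome names the same test for the analysis: "The exact Cochran-Armitage trend test will be used for the primary outcome".
- Interim analyses plans one look on at least 60 patients at SC week 12, after which the choice is to "either stop the study for futility or to go on as planned". It gives no threshold, and the Sample size section does not mention the look.
- Trial status reports that "289 patients have been screened, and 172 have been randomized".

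**The concern.** The article gives the test, error rate, rates, sample size and power together, so they can be checked against each other without any other document. They do not quite agree. Power is the main planning figure: at 87.9% the risk of missing the assumed effect is 12.1%, not 10%.

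Two neighbouring points affect how the figure is read. The text does not say outright whether the 15%/10% mixture is already inside the three rates. Nor does it say whether the 90% was meant before or after the futility look.

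**Working it through.** **Inputs.** n = 58 per arm; rates 0.65 (placebo), 0.52 (low), 0.35 (high); equally spaced scores; one-sided 0.025. Withdrawal counts as an endpoint, so no separate dropout inflation applies.

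**Statistic.** With equal arms and equally spaced scores, the trend statistic reduces to D = failures on placebo minus failures on high dose. The low-dose arm enters only through the total number of failures.

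**1. Reproducing the plan's figure with the asymptotic test.** The mean rate is (0.65 + 0.52 + 0.35)/3 = 0.5067.

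- Expected D: 58 × (0.65 − 0.35) = 17.4
- Critical value: 1.96 × √(2 × 0.5067 × 0.4933 × 58) = 1.96 × 5.385 = 10.55
- SD of D under the alternative: √(58 × (0.65 × 0.35 + 0.35 × 0.65)) = √26.39 = 5.137
- Power: Φ((17.4 − 10.55)/5.137) = Φ(1.333) = 90.9%

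Solving the same formula for 90% gives n = 56.3, so 57 per arm. The stated 58 is therefore within one patient per arm of an asymptotic calculation.

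**2. The exact test as named.** All outcomes of the three binomials were enumerated, and each was rejected if the conditional one-sided p-value, given total failures, was at most 0.025.

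| n per arm | Exact power | Asymptotic test, enumerated |
|---|---|---|
| 56 | 89.3% | 89.3% |
| 57 | 90.2% | 90.2% |
| **58** | **87.9%** | **90.9%** |
| 59 | 88.4% | 91.7% |
| 60 | 89.3% | 92.3% |
| 61 | 90.1% | 92.9% |
| 62 | 90.8% | 93.5% |

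Over the range checked (52 to 71), 57 is the smallest n that reaches 90%. From 61 upward, power stays above 90%.

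**3. Why 58 dips.** Expected total failures at 58 per arm are 58 × 1.52 = 88.

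- n = 57, 86 failures: D = 11 has p = 0.0247, so 11 is enough.
- n = 58, 88 failures: D = 11 has p = 0.0257, so 12 is needed (p = 0.0164).

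One more patient per arm raises the required difference by a whole unit. At 58 and a common rate of 0.5067, the test's actual size is about 1.75%.

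**4. Sensitivity to rounding of the rates, exact test, n = 58.**

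- 65.4/52/34.6%: 89.7%
- 65.5/52/34.5% (the limit of rounding): 90.1%
- 66/52/35%, or 65/52/34%: 90.1%

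**5. If the 15%/10% mixture still had to be applied.** The formula is 0.85 × rate + 0.15 × 0.10:

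- placebo 0.5525 + 0.015 = 56.75%
- low dose 0.442 + 0.015 = 45.7%
- high dose 0.2975 + 0.015 = 31.25%

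Exact power at 58 would then be 76.9% (asymptotic 79.8%).

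**6. The 172 actually randomized.** The article does not give the split. Assuming two arms of 57 and one of 58, exact power is 88.8% if the larger arm is placebo or high dose, and 90.2% if it is low dose.

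**The case against.** The strongest reply is that nothing of substance is wrong. The exact test reaches 90% at 57, one patient per arm below the plan. The shortfall at 58 comes from discreteness alone and vanishes within rounding of rates that are given in whole percents and adapted from an earlier study. The Study protocol amendments section describes planning assumptions that mix patients recruited before and after Amendment 3 and apply different dropout rates, so the unrounded rates may well not have been whole numbers. The low actual size is a property of the named test and protects the type I error. Recruitment is also complete. All of this stands, and it is why the point is minor. It does not make 90% the right figure for the inputs as printed.

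Three stronger readings are tempting, and the documents support none of them.

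- **The trial is too small.** A reader might infer that 61 per arm was needed. The result at 57 and the sensitivity to rounding show that 58 is not materially wrong.
- **The futility look was ignored and costs a known amount of power.** The article states no allowance, but it condenses a fuller protocol that may contain one. A stop that is followed can only lower power. By how much depends on a threshold that is not given, so any figure would describe an invented rule.
- **True power is 77%.** This needs the 15%/10% mixture to come on top of the three rates. The article presents those rates as the percentages of patients reaching the endpoint, which naturally means all patients, and 58 comes close to 90% only on that reading.

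**Conclusion.** The point holds as a minor inconsistency in the stated power. With the printed inputs, the exact test at 58 per arm has 87.9% power, 2.1 points below the stated 90%. This takes 35/52/65% as all-patient rates, assumes equal arms, and is before any futility stop. Neither the sample size nor the primary test needs to change. The all-patient reading of the rates is the natural one but is left implicit, and since the alternative would mean about 77%, it should be stated. For the futility look, the documents support only the direction of the effect.

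**What to change.** In the Sample size section:

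1. Restate the power as about 88% for the exact test at 58 per arm, before any futility stop. Alternatively, keep 90% and print the unrounded rates that produce it.
2. Add one sentence confirming that 35/52/65% are rates among all randomized patients and already include the 15% IVIg-independent patients. If they do not, state about 77%.
3. Say that the figure does not account for the futility look or, if the full protocol fixes the threshold, give the power with the rule applied.

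The cost is a few words of text and a slightly less favourable headline figure. It needs no extra patients. Replacing the conditional exact test with an unconditional one would be a matter of preference and is not needed. Declaring the futility rule non-binding would not restore power if the rule were followed.

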#### General considerations

Analyses will be based on the following populations: total set, safety data set (SDS), pre-randomization safety data set (PSDS), intention-to-treat set (ITTS), per protocol set (PPS), and rescue safety data set (RSDS). A blind data review meeting will be arranged to discuss all protocol deviations to decide which patients will be excluded from certain analyses. A reference visit is defined per study period, and this visit is used to assess changes within the period using summary statistics (Table 1). All analyses will be done using SAS® version 9.1.3 (SAS Institute Inc., Cary, NC) or higher.

**Table 1 Tab1:** Definition of reference visit and last visit of study periods

Period	First visit of period	Reference visit(s) of period	Last visit	
IgG dependency	Screening	Prior to AMD3: INCAT. After AMD3: INCAT: day 14 phone call I-RODS / mean grip strength: peak value within first 4 weeks	Week 1 day 1, before start of IVIg infusion	…or last visit before/at withdrawal
IVIg restabilization	Week 1 day 1 at start of IVIg infusion	Week 1 day 1 at start of IVIg infusion. If not available, last visit of IgG Dependency Period	SC week 1 before start of SC infusion	
SC treatment	SC week 1 at start of SC infusion	Baseline (week 10/13)	Week 25 visit or first IVIg infusion for rescue before IVIg infusion	
IVIg rescue	first IVIg infusion for rescue at start of IVIg infusion	First IVIg infusion for rescue at start of IVIg infusion	Completion visit	

*IgG* immunoglobulin G, *INCAT* Inflammatory Neuropathy Cause and Treatment, *IVIg* intravenous immunoglobulin, *I-RODS* inflammatory-Rasch-built overall disability scale, *SC* subcutaneous

#### Efficacy evaluation primary outcome

The exact Cochran-Armitage trend test will be used for the primary outcome. This comparison will be calculated to test for superiority of at least one IgPro20 dose over placebo at a one-sided type-I error of α = 0.025. If the hypothesized superiority is demonstrated, one-sided Fisher’s exact tests will be used for the subsequent comparisons: placebo vs. low dose IgPro20, and low dose IgPro20 vs. high dose IgPro20.

The proportions and corresponding two-sided 95 % Wilson-Score confidence intervals will be calculated for each treatment group. Point estimates for the difference in proportions and the corresponding exact two-sided 95 % confidence intervals will be calculated for all pair-wise treatment comparisons. The primary endpoint analyses, including all sensitivity analyses (see below), will be performed based on the ITTS and repeated for the PPS.

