#### Sensitivity analyses

Sensitivity analyses will be performed with modified primary endpoint definitions to investigate the potential bias due to the inclusion of dropouts without CIDP relapse (patients who withdraw from the study due to any reason other than CIDP relapse) in the primary endpoint. For each sensitivity analysis, the analysis performed for the primary endpoint will be repeated, including the exact Cochran-Armitage trend test, one-sided Fisher’s exact tests for the pair-wise treatment comparisons and all estimates and confidence intervals.

For the primary analysis, only patients who complete the study without recording a relapse are considered nonrelapsers. All other patients, including those who withdraw for any reason other than relapse, are considered relapsers. Four sensitivity analyses will be performed that assign a different status’ (relapse or nonrelapser) to patients who are withdrawn from the study for reasons other than efficacy (Table 3):

**Table 4 Tab4:** Subgroup analyses by endpoint

Subgroup	Primary efficacy analysis of Relapse rate	INCAT total score	Mean grip strength (dominant/ nondominant hand)	I-RODS	MRC sum score	Time to relapse or withdrawal for any other reason	IgG serum levels
Sex (male/female)	X	X	X	X	X	X	
Age group (≥18 years to ≤ 65 years, and > 65 years)	X	X	X	X	X	X	
Prestudy IVIg treatment modality (IVIg maintenance therapy, acute IVIg therapy)^a^	X	X	X	X	X	X	
Region (Japan/non-Japan)	X						X
Relapse status (yes/no)							X
IVIg Dependency criterion: I-RODS or grip strength	X^b^						

*IgG* immunoglobulin G, *INCAT* Inflammatory Neuropathy Cause and Treatment, *IVIg* intravenous immunoglobulin, *MRC* Medical Research Council, *I-RODS* Inflammatory-Rasch-built Overall Disability Scale

^a^For Japanese subjects only

^b^This subgroup analysis will only be conducted if the group size is ≥ 30

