### Study protocol amendments

During the conduct of this trial, the protocol has been amended five times. Amendments 1 and 2 (17 Nov 2011 and 10 Dec 2012) addressed only local changes and Amendment 5 (15 Sep 2015) was mainly to update safety information. With Amendment 3 and 4 (12 Apr 2013 and 11 Sep 2014), the following two important changes were implemented:

(1) The IVIg withdrawal phase was modified to an IgG dependency test and additional deterioration criteria were implemented as described above. Fulfillment on one of these criteria, in the event of an unchanged INCAT score, qualified the patient to move to the next study phase (Amendment 3). Relapse rates in the IgPro20 groups were anticipated to increase after this change due to the fact that significant decrease in grip strength (i.e., 8-point deterioration) is not always accompanied by a corresponding worsening in adjusted INCAT score by 1 point [40]. To correct for the new assumptions for relapse percentages underlying the power calculation, the sample size was increased from 150 to 174, and the screening numbers were increased from 250 to 350. The underlying assumptions were that 90 % of subjects would be recruited after Amendment 3 and the dropout rates for placebo subjects would increase to 15 % (while being around 10 % in the active treatment groups).

(2) The length of time required for prestudy IVIg has been reduced to 8 weeks (Amendment 4). The change in this requirement is not expected to adversely affect the outcomes of the SC treatment period because all patients must show IgG dependency (up to 12 weeks) and IVIg restabilization (up to 13 weeks) before randomization and start of SC treatment.

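### The primary trend test and crude risk differences leave out the IgG-dependency entry criterion: a possible, conditional loss of efficiency, not an error of validity

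*Protocol article*

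**What the plan says.** - **Primary test** (Efficacy evaluation primary outcome): "The exact Cochran-Armitage trend test will be used for the primary outcome", one-sided at 0.025, followed by one-sided Fisher tests. Confidence intervals are given for the crude pairwise differences in proportions. No stratum or covariate is named.
- **Sample size**: "The exact Cochran-Armitage trend test with equally spaced scores has been used for the sample-size calculation". At one-sided 2.5 % the article arrives at 58 patients per arm for 90 % power. The assumed failure rates are "35 % for the IgPro20 high dose, 52 % for the IgPro20 low dose, and 65 % for placebo".
- **Entry routes** (IgG dependency test period; Study protocol amendments): since Amendment 3 a patient can qualify through I-RODS or grip strength while INCAT is unchanged. The reason given for revising the relapse assumptions is that a "significant decrease in grip strength (i.e., 8-point deterioration) is not always accompanied by a corresponding worsening in adjusted INCAT score by 1 point". The same sentence says that relapse in the IgPro20 groups was therefore expected to rise. The sample size went from 150 to 174.
- **Endpoint** (Primary outcome): a rise of at least 1 point in adjusted INCAT, or withdrawal from the study.
- **Randomisation** (Randomization and masking): stratified by region only.
- **Other use of the criterion** (Table 4): "IVIg Dependency criterion: I-RODS or grip strength" is an exploratory subgroup for the primary endpoint, run only if the group has at least 30 patients.
- **Log-rank tests** (Table 2, footnote c; sensitivity analysis D): no strata named. Where a covariate is intended the article names it, as with region in the ANOVA (footnote d).

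**The concern.** The trial randomises two kinds of patient: those whose INCAT rose when IgG was withheld, and those who lost only grip strength or I-RODS. The relapse part of the endpoint is itself an INCAT rise. The article says that the second kind of loss need not bring an INCAT loss, and it thought the difference important enough to change the sample size. The entry criterion is therefore a natural candidate to predict the endpoint, and it is already recorded.

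If it does predict the endpoint, a test that leaves it out counts explainable variation as noise. Because the criterion is not a randomisation stratum either, a chance difference in its mix between arms passes into the crude placebo-minus-IgPro20 difference. At stake are some power and some precision.

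**Working it through.** **Inputs from the article.** 58 per arm; one-sided 2.5 %; scores 2, 1, 0 for placebo, low dose and high dose; failure 65/52/35 %.

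**Inputs assumed, because the article does not give them.** The share *f* of randomised patients who qualified on I-RODS or grip strength only (10–50 %), and the odds ratio OR for failure, INCAT-qualified versus the others (1–5). Overall rates stay at 65/52/35 % throughout.

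**1. The plan's own figure.** Full enumeration at 58 per arm gives power 87.9 % for the exact test (actual size 1.75 % at a common rate of 50 %) and 90.9 % for both the mid-p and asymptotic versions. The exact test reaches 90.15 % at 57 per arm; its power is not monotone in n because the statistic is discrete. So 58 for 90 % is reproduced to within that discreteness.

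**2. Stratified exact test.** In stratum s, given m_s failures,

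P(T_s = t) = Σ C(n_s0, a)·C(n_s1, b)·C(n_s2, c) / C(n_s0+n_s1+n_s2, m_s), over a+b+c = m_s and 2a+b = t.

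The p-value is P(T_1 + T_2 ≥ observed), from the convolution of the two strata.

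Example of the split at f = 30 %, OR 3: INCAT-qualified 72.7/60.0/41.7 %, others 47.0/33.3/19.3 %. Check for placebo: 0.7 × 72.7 + 0.3 × 47.0 = 65.0.

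**3. Power, exact test (simulated).**

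| Scenario | Unstratified | Stratified | Gain (points) |
|---|---|---|---|
| f 30 %, OR 1 | 88.1 | 88.7 | 0.5 |
| f 30 %, others 65/58/45 % (relapse higher on IgPro20) | 88.7 | 89.4 | 0.7 |
| f 30 %, OR 2 | 88.0 | 89.6 | 1.6 |
| f 15 %, OR 3 | 88.4 | 90.1 | 1.7 |
| f 20 %, others 40/33/25 % | 87.2 | 89.1 | 1.9 |
| f 30 %, others 45/36/25 % | 88.6 | 91.4 | 2.8 |
| f 30 %, OR 3 | 87.6 | 90.6 | 2.9 |
| f 50 %, OR 3 | 87.8 | 90.8 | 3.0 |
| f 30 %, OR 5 | 88.1 | 92.8 | 4.7 |

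Odds-ratio rows use 12,000 trials (error about 0.3 point per power figure); the other rows use 4,000. The overall rates are the same in every row, so the true unstratified power is 87.9 % throughout and the scatter in that column is simulation error. In the second row the INCAT stratum has (65 − 0.3 × 65)/0.7 = 65 %, (52 − 0.3 × 58)/0.7 = 49.4 % and (35 − 0.3 × 45)/0.7 = 30.7 %.

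**4. Power gain, asymptotic test** (400,000 trials per cell, f 10–50 %): OR 1, −0.2; OR 2, 0.0 to +0.4; OR 3, +0.3 to +1.5; OR 4, +0.5 to +2.4; OR 5, +0.8 to +3.1. For the second row above it is nil (90.85 % against 90.8 %, 300,000 trials for the other rows of this kind).

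**5. Type I error.** In simulation the exact test rejects in 1.6 % of null trials unstratified and 2.0 % stratified, both below 2.5 %.

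**6. Effect estimate.** SD of the difference in shares between two arms = √(2f(1−f)/58). At f = 30 % this is √(0.42/58) = 8.5 points. At OR 3 the stratum gaps are 72.7 − 47.0 = 25.7 (placebo) and 41.7 − 19.3 = 22.4 (high dose), mean about 24, so one SD of imbalance moves the crude difference by 0.24 × 8.5 ≈ 2.0 points. Over f 15–50 % and OR 2–5 the shift is 1.0 to 3.2 points, against a planned difference of 65 − 35 = 30. The crude estimator averages 0.300, so it is unbiased. Adjustment lowers its SD from 0.0886 to 0.0865 (f 30 %, OR 3) or 0.0842 (f 30 %, OR 5).

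**The case against.** **The direction is not the plan's.** A reader might infer from the grip-strength remark that the plan itself says I-RODS/grip-only patients fail less often. It does not: it expects more relapse on IgPro20 after the change. Under that pattern the covariate yields nothing on the asymptotic test and 0.7 point on the exact one. This stands.

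**A fixed loss of 2–3 points is not established.** A reader might also quote that as what the plan gives up. It needs a share and failure rates that the article does not state. The article's one numerical prognostic group, 15 % IVIg-independent patients ("those patients are believed to have a relapse rate of 10 % regardless of treatment"), cannot supply them: it is unobserved and is not the entry criterion. This stands.

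**Part of the exact-test gain is reduced discreteness.** The exact test gains about half a point even at OR 1, and at f 30 %, OR 3 the asymptotic gain is 1.15 points against 2.9. A mid-p test without strata already reaches 90.9 %. This stands too.

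**Prognostic strength may be weak.** Grip strength is self-assessed daily but INCAT is collected every two weeks, so the criterion partly records which instrument triggered first. All randomised patients have also returned to their screening INCAT and been stable, and withdrawals count as failures. This is a fair reason to expect a modest odds ratio; the documents cannot settle it.

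**It is already covered, and validity is intact.** Table 4 does examine the criterion, so the plan as a whole does not ignore it. But an exploratory breakdown by arm, dropped below 30 patients, neither recovers power nor adjusts the estimate. The inference that chance imbalance biases the result is unsupported: it adds variance, which the confidence interval already covers.

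**Conclusion.** The point holds as one of efficiency. The primary trend test and the crude differences leave out a recorded pre-randomisation variable that the article connects to its relapse assumptions. The test is valid, the estimate is unbiased and the stated sample size stands.

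The size is conditional on unstated quantities. With overall rates at 65/52/35 % and 58 per arm, the exact test gains about 0.5–0.7 point if the criterion is not prognostic or acts as the amendment text expects. It gains about 2–3 points at OR about 3 with a share of 30–50 %, and up to about 4.7 points at OR 5. The asymptotic test gains about −0.2 to +3 points over OR 1–5. No exact-test scenario lost power. With recruitment closed at 172 randomised (Trial status), the analysis is the remaining place to recover any.

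**What to change.** Before unblinding:

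1. Specify the exact Cochran-Armitage trend test stratified by dependency criterion (INCAT rise; I-RODS or grip strength only), with patients enrolled before Amendment 3 in the INCAT stratum.
2. Stratify the log-rank tests, overall and pairwise, in the same way.
3. Report stratum-adjusted risk differences, for example Mantel-Haenszel, beside the crude ones. Stratifying the tests alone would leave the effect estimates exposed to chance imbalance.

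If the sponsor prefers to keep the unstratified test as primary, prespecify items 1–3 as the main supportive analysis.

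**Cost.** Analysis wording and one existing variable in the program; no new data. The drawbacks are a late change to the wording of the analysis, which should be documented as made blind, and little or no gain if the criterion proves not to be prognostic.
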